## Abstract

**Background:**

Problem anger is common after experiencing a traumatic event. Current evidence-driven treatment options are limited, and problem anger negatively affects an individual’s capacity to engage with traditional psychological treatments. Smartphone interventions hold significant potential in mental health because of their ability to deliver low-intensity, precision support for individuals at the time and place they need it most. While wearable technology has the capacity to augment smartphone-delivered interventions, there is a dearth of evidence relating to several key areas, including feasibility of compliance in mental health populations; validity of in vivo anger assessment; ability to predict future mood states; and delivery of timely and appropriate interventions.

**Methods:**

This protocol describes a cohort study that leverages 10 days of ambulatory assessment in the form of ecological momentary assessment and a wearable. Approximately 100 adults with problem anger will complete four-hourly in vivo mobile application-delivered micro-surveys on anger intensity, frequency, and verbal and physical aggression, as well as other self-reported mental health and wellbeing measures. Concurrently, a commercial wearable device will continuously record indicators of physiological arousal. The aims are to test the feasibility and acceptability of ambulatory assessment in a trauma-affected population, and determine whether a continuously measured physiological indicator of stress predicts self-reported anger intensity.

**Discussion:**

This study will contribute new data around the ability of physiological indicators to predict mood state in individuals with psychopathology. This will have important implications for the design of smartphone-delivered interventions for trauma-affected individuals, as well as for the digital mental health field more broadly.

## Introduction

More than 70% of adults will experience a traumatic event in their lifetime [1]. Problem anger is one of the most common mental health issues in individuals who have experienced trauma, and is characterised by difficulties recognising early physiological and emotional signs of anger (including altered physiological arousal), swift escalations of affective states, and problems engaging adaptive coping strategies to prevent anger from becoming overwhelming [2]. Problem anger in trauma-affected populations (sometimes referred to as ‘posttraumatic anger’; [3] is often overlooked and rarely addressed relative to other posttraumatic mental health concerns, despite affecting up to 30% of individuals [4, 5]. Problem anger has significant behavioural, social and occupational impacts, including strong links with suicide [5]. Current anger treatments focus on cognitive behavioural therapy (CBT) principles of improving emotional regulation through increased self-awareness and tailored anger control plans that can shift the individual towards greater internal focus and awareness of escalating emotional states, coupled with adaptive coping strategies [6]. Psychotherapy process research has found that of the various CBT components delivered in anger treatments, arousal calming skills consistently predicts improvement [7]. However, such treatments are typically delivered in weekly psychotherapy formats and are associated with high levels of patient drop-out and modest outcomes, in part due to the hostile and irritable nature of individuals with problem anger and the effect of this on the therapeutic alliance [8]. A review on anger management approaches concluded that there is a need for better understanding of characteristics that may impede therapeutic change, in order to refine current treatments, and develop innovative approaches to intervention [9].

Digital mental health interventions offer promise to individuals with problem anger. Recent research has shown that CBT principles can be effectively delivered via smartphone to individuals with problem anger [10], and that longitudinal smartphone-based studies are feasible in individuals with problem anger [11]. Previous research in problem anger has also shown that anger varies frequently on a moment-to-moment basis and, like other affective states, is ecologically influenced. This creates an opportunity for personalised digital interventions such as just-in-time adaptive interventions [12], which have the goal of delivering support “at the moment in the context that the person needs it most and is most likely to be receptive [13]”. In addition to smartphone delivery, modern technology can facilitate multimodal ambulatory assessment and peripheral physiology metrics that can integrate detailed self-report data via ecological momentary assessment with objective, passively collected sensor data through smartphones and wearables. The combined data may provide rich, ecologically valid, contextual, and biopsychosocial information about mental health issues, including temporal information about the dynamics of psychological phenomena [14]. As such, there is the potential for wearable technology to be leveraged to reliably predict and subsequently alter mood states [15]. Given the preliminary findings relating to the potential for digital mental health to address problem anger, coupled with advances in wearable and smartphone technology, the primary aims of this study are to:

Investigate the feasibility and acceptability of the use of a commercial wearable to capture physiological data in a trauma-affected population.Determine whether high levels of self-reported anger intensity can be predicted from physiologically measured stress.

Secondary aims from this study will be exploratory in nature. We will examine relationships among common associated features of problem anger such as pain, alcohol use, sleep, and anger rumination, as well as physiological variables collected from the wearable such as heart rate, inter-beat-interval, location, and steps. The findings from this study will provide world-first evidence for the feasibility of ambulatory assessment (i.e., smartphone and wearable) of physiological and emotional aspects of dysregulated mood in trauma-affected individuals, to inform the development of digital mental health tools.

## Materials and methods

### Participants

Adults aged over 18 with problem anger who have experienced a previous traumatic event will be recruited from around Australia (see Table 1). Participants will be recruited through the researcher’s participant database of trauma-exposed individuals, as well as targeted social media adverts.

**Table 1 pone.0278926.t001:** Study inclusion and exclusion criteria.

Inclusion	Exclusion
≥18 years	Have a recent history of significant violence
Problem anger (≥12 points on the 5-item Dimensions of Anger Reactions Scale)	Physical health conditions affecting the cardiovascular system
Experienced a previous traumatic event (endorsement of a DSM-5 Criterion A event)	Unwilling to use the wearable for 10 days
Own an internet-connected smartphone	

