### Power and sample size

The total feasible sample size is ~100 participants due to the expense of wearables. Specific sample size details for Aim 1 and 2 are described below.

For Aim 1, a target of a minimum of 75% of participants reporting satisfaction with ease of use of the wearable and app, and low frustration is set. A total feasible sample size of 100 participants would ensure that the precision of the two-sided 95% confidence interval of the true underlying proportion of participants who adhere to the intervention is at most +/- 9% when assuming a proportion of 75% using the Wald method to measure the 95% confidence interval.

For Aim 2, a sample size of 100 participants provides a total of 4000 possible outcome observations since each participant has 40 measurement occasions. It is assumed that up to 30% of these observations will be missing [11], resulting in 2800 possible observations (approximately 28 per participant) and that 25% of recorded outcomes will be high intensity anger (≥ 7). The design effect is estimated to be 14, assuming an intraclass correlation of 0.48 from prior data, which leads to an effective sample size of 200 for this study if 100 participants are recruited. Sample size calculations for prediction modelling were conducted according to the three criteria (shrinkage, overfitting and precision; [16]. An effective sample size of 200 results in the ability to detect a minimum Cox-Snell R^2^ of approximately 0.04 assuming one predictor (physiologically recorded stress; 1–100) and ensuring the shrinkage is the recommended 0.9. This sample size satisfies the overfitting criteria for a maximum possible Cox-Snell R^2^ of 0.53, according to estimates of the null model log-likelihood and provides a margin of error of 0.06, marginally higher than the more stringent 0.05 but below the required 0.1.

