#### Primary outcomes

For Aim 1, acceptability, feasibility, adherence, and usability will be measured using a mixed methods approach. Acceptability and usability will be collected from participants at Time 3, using quantitative self-report measures of ease of use (1; Very Difficult to 5; Very easy), ease of understanding (1; Very Difficult to 5; Very easy), and levels of frustration with the study protocol (1; Very Frustrating to 5; Not at all), as well as qualitative responses to strengths and limitations of the protocol. Feasibility and adherence will be determined using missing data patterns for both wearable and EMA data, and number of support calls required.

For Aim 2, an EMA measure of anger intensity (*Rate the overall intensity of the anger or irritability you feel right now*; 10-point Likert Scale ‘1’ Lowest intensity; ‘10’ Highest intensity), and wearable data related to physiological indictor of stress (1–100) will be used (see sections below for more details).

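### Aim 1 asks about acceptability in trauma-affected people, but the sample is restricted to those already willing to wear the device and uptake is not a listed outcome

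*Protocol article*

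**What the plan says.** The Introduction gives as the first primary aim to study the "feasibility and acceptability of the use of a commercial wearable to capture physiological data in a trauma-affected population". The Discussion repeats this as a primary question about trauma-affected populations. Neither place restricts the statement to people prepared to wear the device.

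Table 1 (Participants) lists among the exclusions "Unwilling to use the wearable for 10 days".

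Under Power and sample size, the only numerical criterion for Aim 1 is that "a target of a minimum of 75% of participants reporting satisfaction with ease of use of the wearable and app, and low frustration is set". The same paragraph gives a precision that "is at most +/- 9% when assuming a proportion of 75% using the Wald method to measure the 95% confidence interval", stated for the proportion who adhere.

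Under Primary outcomes, "Acceptability and usability will be collected from participants at Time 3", and "Feasibility and adherence will be determined using missing data patterns for both wearable and EMA data, and number of support calls required". Uptake, or refusal of the device, is not on the list.

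**The concern.** Declining to wear a device is one of the most direct signs that it is not acceptable. The plan removes people who decline before enrolment and lists no outcome that counts them. The sample is thus selected on part of what Aim 1 sets out to study, while the aim and the planned conclusion are worded for the wider population.

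At stake is the inference that the article itself wants to draw, namely whether tools of this kind can be developed for trauma-affected people. A study could meet the 75% target while an appreciable share of otherwise eligible people had refused the device, and no listed Aim 1 result would show it.

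A second, weaker issue is that the ratings are taken after the 10-day period. Someone who does not answer at Time 3 has no rating, so the reported proportion may depend on how such people are counted.

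**Working it through.** **The plan's own figure.** Inputs from Power and sample size: proportion 0.75, n = 100, two-sided 95% Wald interval. Half-width = 1.96 × √(0.75 × 0.25 / 100) = 0.085, so the stated bound of 9 points reproduces. It is stated for adherence, which comes from device and EMA data, so it implies no required number of Time 3 responders and plays no further part here.

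**Step 1: who is described.** Set the sections side by side:
- Aim (Introduction, Discussion): trauma-affected population, without a limit on willingness.
- Sample (Table 1): people with problem anger and a qualifying trauma, less those unwilling to wear the device.
- Listed feasibility measures (Primary outcomes): missing-data patterns and support calls, both observed only after enrolment.

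No listed measure covers the step from eligible apart from willingness to enrolled.

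**Step 2: what an uptake figure would add.** Let u be the share of otherwise eligible people excluded only for unwillingness. The article gives no value; 10% to 30% is an assumed range. Uptake = enrolled / (enrolled + excluded only as unwilling) = 1 − u. If 75% of the enrolled are satisfied, the share of all these people who are both willing and satisfied is 0.75 × (1 − u).

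| u (assumed) | Excluded per 100 enrolled, 100u/(1 − u) | Uptake | Willing and satisfied |
|---|---|---|---|
| 0% | 0 | 100% | 75.0% |
| 10% | 11 | 90% | 67.5% |
| 20% | 25 | 80% | 60.0% |
| 30% | 43 | 70% | 52.5% |

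The last column is a different quantity from the 75% target, because people who never used the device cannot rate its ease of use. It shows only how much the target leaves unsaid about the population named in the aim.

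**Step 3: Time 3 response.** Let p be the true satisfied proportion among the enrolled, and let rs and ru be the Time 3 response rates of satisfied and unsatisfied participants. The article gives none of these; all are assumed. The proportion seen among responders is p·rs / (p·rs + (1 − p)·ru). With p = 0.70:
- rs = ru: 70%, no bias.
- rs = 0.95, ru = 0.80: 0.665 / 0.905 = 73.5%.
- rs = 0.95, ru = 0.70: 0.665 / 0.875 = 76.0%, above the target although the true value is below it.
- rs = 0.95, ru = 0.50: 0.665 / 0.815 = 81.6%.

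With all enrolled as denominator and non-responders counted as not satisfied, each case with rs = 0.95 gives 0.70 × 0.95 = 66.5%, which is below the true 70%. That figure is a lower bound, not an unbiased estimate. In these cases the two figures together bracket the truth.

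**The case against.** A reader might infer that the 75% target is itself biased towards success. The article does not support that, for four reasons.

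- **The exclusion does not distort the ratings.** Ease of use and frustration can be rated only by people who have used the device. Leaving out those who refuse changes whom the estimate applies to, not its validity among users. A person unwilling to wear the device would hardly consent to a 10-day wearable study, so the criterion largely formalises consent. This stands, and it is why the point concerns the scope of the conclusion.
- **A responders-only denominator is not stated.** The target refers simply to participants, and an all-enrolled denominator fits that wording as well. A person who stops wearing the device could still complete the online Time 3 survey and report frustration there. An article may also leave this detail to the full protocol or analysis plan. This stands: any bias from Time 3 loss is conditional on dissatisfied people responding less.
- **Abandonment would not be hidden.** Missing wearable and EMA data are listed Aim 1 measures and do not depend on the Time 3 survey. This stands for people who enrol and then stop. It does not cover people who were never enrolled.
- **Counting every non-responder as dissatisfied is a worst case.** It can push the estimate too low, as Step 3 shows. This stands, so it belongs in a sensitivity analysis and not in the primary result.

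None of these answers the mismatch between the population in the aim and the population in Table 1, or the absence of uptake from the listed measures.

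**Conclusion.** The concern holds as a limit on what Aim 1 can conclude. As planned, the 75% target describes people with problem anger after trauma who were already willing to wear the device for 10 days, whereas the aim and the Discussion speak of trauma-affected populations generally. The mismatch rests on stated text alone and needs no assumption.

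Its size cannot be derived from the article. The range of 90% to 70% for uptake, and of 67.5% to 52.5% for willing and satisfied, depends entirely on the assumed refusal share of 10% to 30%. With no refusals there is no gap. The Time 3 issue is secondary and conditional: a true 70% could appear as 73.5% to 81.6% under the unequal response rates assumed above, and as exactly 70% if response does not depend on satisfaction.

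**What to change.** 1. Keep the exclusion criterion. Record at screening how many people are excluded for unwillingness alone.
2. Add uptake = enrolled / (enrolled + excluded only as unwilling) to the Aim 1 feasibility results and report it beside the 75% target. It will still miss people who saw the recruitment material and did not come forward because of the device, so describe it as uptake among those screened.
3. Word the acceptability conclusion for people willing to wear the device.
4. Report the satisfied proportion among Time 3 responders and, as a lower-bound sensitivity analysis, the proportion over all enrolled with non-responders counted as not satisfied.

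The cost is a screening count and a few sentences, with no further data from participants. About 15% of the desired sample had completed the study at the time of writing. The article does not say whether reasons for exclusion were recorded for people already screened; if they were not, the uptake figure should state the date from which it counts. The headline may become less favourable.

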### Study design

This study is a cohort study using ambulatory assessment (i.e., ecological momentary assessment and a wearable; Garmin Vivofit 4), with data collected at three time points: Time 1: pre-ambulatory self-report surveys; Time 2: ambulatory assessment (for a 10-day period); and Time 3: post-ambulatory self-report surveys and qualitative interviews. Self-report surveys will be completed online using REDCap. Ambulatory assessment data will be collected by participants using a commercial wearable and a customised study app (mEMA-sense), in conjunction with their own personal Android or Apple smartphone. This is an Australia-wide study with data analyses occurring in Melbourne, Australia. As this is a study protocol, no data has been included, conforming to the PLOS data policy.

### Power and sample size

The total feasible sample size is ~100 participants due to the expense of wearables. Specific sample size details for Aim 1 and 2 are described below.

For Aim 1, a target of a minimum of 75% of participants reporting satisfaction with ease of use of the wearable and app, and low frustration is set. A total feasible sample size of 100 participants would ensure that the precision of the two-sided 95% confidence interval of the true underlying proportion of participants who adhere to the intervention is at most +/- 9% when assuming a proportion of 75% using the Wald method to measure the 95% confidence interval.

For Aim 2, a sample size of 100 participants provides a total of 4000 possible outcome observations since each participant has 40 measurement occasions. It is assumed that up to 30% of these observations will be missing [11], resulting in 2800 possible observations (approximately 28 per participant) and that 25% of recorded outcomes will be high intensity anger (≥ 7). The design effect is estimated to be 14, assuming an intraclass correlation of 0.48 from prior data, which leads to an effective sample size of 200 for this study if 100 participants are recruited. Sample size calculations for prediction modelling were conducted according to the three criteria (shrinkage, overfitting and precision; [16]. An effective sample size of 200 results in the ability to detect a minimum Cox-Snell R^2^ of approximately 0.04 assuming one predictor (physiologically recorded stress; 1–100) and ensuring the shrinkage is the recommended 0.9. This sample size satisfies the overfitting criteria for a maximum possible Cox-Snell R^2^ of 0.53, according to estimates of the null model log-likelihood and provides a margin of error of 0.06, marginally higher than the more stringent 0.05 but below the required 0.1.

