#### Statistical analyses

For Aim 1, descriptive analyses of quantitative measures of acceptability, feasibility, adherence, and usability will be conducted and mean, range and median responses to questions reported. Qualitative data collected from interviews with participants will be synthesised.

For Aim 2, continuously measured physiological stress (Garmin formula [17]; score 1–100) captured by wearable sensors will be examined as a predictor of self-reported anger intensity (1–10). Values recorded in the 10-minute interval prior to the EMA micro-survey will be extracted for use in the prediction models.

Descriptive analyses will be performed on the data to determine missingness, completion rates, outliers and erroneous values, and a proxy for wear time of the wearable sensor, e.g. time between first and last values each day [18]. The following analysis methods that can handle predictors that have been continuously measured prior to each longitudinal outcome measurement will be considered: i) two-stage approaches where appropriate features (maximum, variance, etc.) of the continuously measured predictors are included in a generalised linear mixed model [18–20]; ii) functional data analysis (FDA) approaches, where the continuously measured predictors are treated as functions when building prediction models [21]. FDA can be implemented in either regression modelling frameworks [22] or machine learning frameworks, such as functional partial least squares [23] and random forests [24]. The predictive performance of each model will be assessed using the balanced error rate (percentage of misclassified momentary anger episodes) calculated using 5-fold cross-validation. Variables importance will also be assessed using metrics suitable for the modelling approach [25].

Additional models, including Dynamic Structural Equation Models (DESM) and Time Varying Effects Models (TVEM), will be built to investigate bi-directional relationships between anger and variables of pain, alcohol, sleep quality, and rumination. Data cleaning and statistical analyses will be performed in SPSS (v23, IBM) and R (R. RStudio, Boston, MA, USA; [26].

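### Aim 1 sets a 75% satisfaction target, states precision for an adherence proportion instead, and names summaries that do not show whether 75% was reached

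*Protocol article*

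**What the plan says.** All references are to the protocol article.

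- **Target (Power and sample size).** The first primary aim carries "a target of a minimum of 75% of participants reporting satisfaction with ease of use of the wearable and app"; the same sentence adds low frustration as a further element. This is a share of participants, defined on ease of use and frustration.
- **Precision (same section, next sentence).** With 100 participants, the "precision of the two-sided 95% confidence interval" is put at no worse than 9 percentage points either side, "when assuming a proportion of 75% using the Wald method to measure the 95% confidence interval". The quantity named is the "true underlying proportion of participants who adhere to the intervention".
- **Measurement (Primary outcomes).** Acceptability and usability come from 1–5 self-report items at Time 3: ease of use, ease of understanding, and "levels of frustration with the study protocol", where 5 means no frustration. Feasibility and adherence come from a different source: missing-data patterns in the wearable and EMA data, and the number of support calls.
- **Analysis (Statistical analyses).** Aim 1 gets descriptive analyses, with "mean, range and median responses to questions reported". The section names no proportion, no confidence interval and no comparison with 75% for this aim.

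**The concern.** The target, the precision statement and the named summaries should all concern the same quantity, and here they concern three. The target is a proportion satisfied and not frustrated. The precision is for a proportion adhering. The summaries describe the location and spread of item scores.

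Feasibility and acceptability is one of the study's two primary aims, and 75% is the only number against which it can be judged. Someone who followed the analysis section to the letter would produce a table that does not say whether that number was reached. The decision on how to count a satisfied participant would then fall after the responses had been seen.

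**Working it through.** **Inputs.** From Power and sample size: proportion 0.75, n = 100, two-sided 95% Wald interval, target at least 75%. From Primary outcomes: 1–5 items at Time 3. From Statistical analyses: mean, range and median. The article gives no cut-point for satisfied; 4 or more is assumed below, and 3 or more is tried as an alternative.

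**1. The plan's own figure.** Wald half-width = 1.96 × √(p(1 − p)/n) = 1.96 × √(0.75 × 0.25/100) = 0.0849, or 8.5 points. The stated bound of 9 points reproduces.

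**2. Does it carry over to the satisfaction proportion?** The formula depends only on p and n, so any 75% proportion in 100 participants has the same half-width. The n needed for 9 points is 1.96² × 0.1875/0.09² = 88.9, so 89. The bound therefore holds for the satisfaction items if at least 89 participants answer at Time 3. With 80 responders the half-width would be 9.5 points.

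**3. Do mean, median and range determine the share scoring 4 or more?** Take 100 answers with range 1–5 and median 4.

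| Answers | Sum | Mean | Median | Share scoring 4 or more |
|---|---|---|---|---|
| 7 ones, 92 fours, 1 five | 7 + 368 + 5 = 380 | 3.8 | 4 | 93% |
| 1 one, 48 threes, 20 fours, 31 fives | 1 + 144 + 80 + 155 = 380 | 3.8 | 4 | 51% |

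The reported line would be identical, yet one set passes 75% and the other fails. Enumerating all such distributions gives these limits:

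| Mean | Lowest share scoring 4 or more | Highest share |
|---|---|---|
| 3.5 | 51% | 83% |
| 3.8 | 51% | 93% |
| 4.0 | 53% | 99% |

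**4. Does this depend on the assumed cut-point?** Not in kind. With 3 or more as the cut, the second set in step 3 has 99% above it. Another set, 1 one, 25 twos, 41 fours and 33 fives, sums to 1 + 50 + 164 + 165 = 380, so it also has mean 3.8, median 4 and range 1–5, but 74% above the cut. The verdict on 75% again differs. The second set in step 3 itself moves from 51% to 99% when the cut moves from 4 to 3, so the cut-point has to be fixed in advance.

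**5. If both conditions must hold in the same person.** Summaries of each item separately cannot give the joint share. Even if exactly 75% met each condition, the share meeting both could be anywhere from 0.75 + 0.75 − 1 = 50% up to 75%.

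**The case against.** Most of the defence stands.

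- **The analysis is not closed to proportions.** A reader might infer that the plan will report nothing but means, ranges and medians and so can never answer the target. The text does not go that far. It promises descriptive analyses and names three summaries without excluding others. The 1–5 items are collected per participant, and naming a Wald interval suggests that a proportion was in mind. The gap is in the stated analysis, not in the data.
- **The interval is not too wide.** A reader might also infer that ±9 points is inadequate because an observed 75/100 gives 66.5% to 83.5%. That does not follow. At an observed 75%, the lower limit lies below 75% at every finite sample size. The article makes a precision statement, not a test against 75%. A lower Wald limit of at least 75% would need 83/100, but the article states no such rule.
- **Adherence belongs to Aim 1.** It is one of four constructs listed for this aim, so giving it a precision statement is legitimate in itself. Calling the protocol an intervention is loose wording with no numerical effect.
- **The missing cut-point is not a fault in an article.** A fuller plan may define it, and whether to use Wald or another interval is a matter of preference.

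These points do not remove the mismatch. The target sentence and the precision sentence name different proportions, and the summaries named for the items do not give the targeted one. A cut-point held in another document would not make these statements agree.

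**Conclusion.** The point holds as an inconsistency between the Aim 1 target, the proportion used for its precision, and the summaries named for its analysis. Followed literally, the plan leaves its only numeric Aim 1 criterion unevaluated: with a mean of 3.8, a median of 4 and a range of 1–5, the share scoring 4 or more can lie anywhere from 51% to 93%. That range assumes 100 responders and a cut at 4; a cut at 3 leaves the same kind of ambiguity.

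No stated figure is wrong. The ±9 points is correct and applies to the satisfaction proportion provided at least 89 participants respond at Time 3. Because the item-level data will exist and the sample size is unaffected, this is a moderate matter of wording and should be corrected, but it does not threaten the study.

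**What to change.** 1. **Statistical analyses.** Add the proportion of participants meeting the satisfaction and low-frustration criterion, with its 95% CI, set against 75%. State the cut-point on the 1–5 items (for example 4–5) and whether both conditions must hold in the same participant. Keep means, medians and ranges as supporting description.
2. **Power and sample size.** Attach the precision sentence to that proportion and remove the reference to an intervention. Note that the 9-point bound needs at least 89 Time 3 responders.
3. **Adherence.** Report it as its own proportion with a CI, using a per-participant definition.
4. **Timing.** Fix these definitions before the Time 3 responses are examined. The article reports that about 15% of the desired sample had already completed the study.

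The choice between Wald and Wilson intervals is optional. The cost is a few sentences in two sections, with no new data and no change in sample size.
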